**Figure 2 F2:**
[figure not shown]
Classification of study endpoint.

### Further classification of treatment failure

Treatment failure will be further classified as:

*Poor azithromycin absorption:* There is no vomiting or diarrhoea reported after treatment but low levels of azithromycin concentration are found in the vaginal cells [30,31] and the MIC for the initial chlamydia culture is within reported range.

*Persistent chlamydia not responding to azithromycin:* Azithromycin absorption shows adequate levels of azithromycin in the vaginal cells, the minimal inhibitory concentration (MIC) for the initial chlamydia culture is within reported range and the subsequent chlamydia culture is negative [13,23,32,33].

*Reduced antimicrobial susceptibility and resistance:* Some viable infectious chlamydia is present when cultured with antibiotic series compared with cultures with no antibiotic series. The MIC for initial chlamydia culture is elevated compared with reported range [13,15,32,34,35]. Evidence of 23S rRNA gene mutation may or may not be present.

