### Recruitment

Women who have tested positive for chlamydia will be seen by a research nurse at a participating clinic at point of treatment. The research nurse will explain the study to them, assess eligibility and take informed consent. The research nurse will collect specimens for further testing (Table 1) and provide treatment with a single dose of 1 gram azithromycin. The nurse will observe the participant as she takes her treatment to ensure compliance. This is classified as the baseline visit (Day 0). All clinic visits, pathology costs and treatment for participants and their partners will be provided free of charge.

**Table 1 T1:** Specimen collection by study timeline.

**Specimen collection and testing**										**If PCR positive @ d28, 42 or 56**
Day	0^d^	7	14	21	28	35	42	49	56	
Number of swabs collected	4	2	2	2	2	2	2	2	2	4-5
Culture	X									X
PCR^a^	X	X	X	X		X		X		X
Chlamydia organism load^a^	X	X	X	X	X	X	X	X	X	X
Genotype^a^	X	X	X	X	X	X	X	X	X	X
Sequencing^a^	X	X	X	X	X	X	X	X	X	X
Y-chromosome^a^		X	X	X	X	X	X	X	X	X
β-globin^a^	X	X	X	X	X	X	X	X	X	X
Test of cure^b^					X		X		X	
Az absorption^a^		X								
Blood	X									X
Rectal swab^c^										X
Location	Clinic^e^	Clinic^e^	Home^f^	Home^f^	Home^f^	Home^f^	Home^f^	Home^f^	Home^f^	Clinic^e^

^a^Processed in batches throughout the course of the study.

^b^Chlamydia PCR done in real time to report results back to participants and treat any women diagnosed chlamydia positive.

^c^If anal sex reported.

^d^Day 0 = baseline or at time of recruitment.

^e^Swabs collected by research nurse and put immediately into the appropriate medium.

^f^Self-collected high-vaginal swabs.

Key: X = specimen processed for this experiment, PCR polymerase chain reaction, Az *absorption* azithromycin absorption, d day.

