### Primary outcome

The primary outcome is the proportion of women who are classified as having chlamydia treatment failure following detection of chlamydia on a self-collected high-vaginal specimen using a polymerase chain reaction (PCR – see below) Specimens will be collected for testing on days 28, 42 or 56 after recruitment (referred to as ‘test of cure’ specimens for the purpose of this study) according to the algorithm in Figure 1. This algorithm follows a previously described method [10] with the addition of the detection of Y chromosome DNA and performing high discriminatory chlamydial genotyping. Y chromosome DNA will be used to validate sexual behaviour data because it can be detected in the vagina for up to 14 days after unprotected intercourse with a male partner [25,26]. Specimens will be collected from participants every 7 days for Y chromosome detection and genotyping will be undertaken on any chlamydia positive specimens collected on days 28, 42 or 56 after recruitment. Chlamydial genotype fingerprinting will be performed to determine any differences in chlamydia strain/serovar between a participant’s baseline specimen and any repeat positive specimens detected at day 28, 42 or 56 [27]. If a woman has the same serovar present at follow up, further testing by multilocus sequence typing (MLST) targeting *ompA* and five house-keeping genes will be undertaken [28,29]. Detection of same MLST type without detection of Y chromosome DNA or any reports of unprotected sex will be classified as treatment failure. If the woman has a different serovar, it will be classified as a re-infection. A repeat positive chlamydia diagnosis will also be classified as a re-infection if the woman’s repeat specimen has the same MLST type and Y chromosome is detected or she reports unprotected sexual contact.

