### Specimen collection and testing

Participants will be asked to return to the clinic for follow up testing at day 7 so that the research nurse can collect further specimens. Thereafter, weekly high-vaginal specimens will be self-collected at home and mailed in a postage-paid envelope to the study centre. Participants will receive weekly short message service (SMS) prompts reminding them to return specimens and questionnaires and will be telephoned if they test chlamydia positive again throughout the study. These women will be requested to attend the clinic for treatment and further specimen collection. Table 1 outlines the number of specimens collected and the tests to be undertaken at each stage of the study.

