## Discussion

Distinguishing between chlamydia re-infection and treatment failure is important to focus treatment recommendations and infection control mechanisms. For example, if most repeat infections in this study are found to be re-infections, then strategies to expedite partner treatment are necessary. If many repeat infections are due to antibiotic treatment failure, then international recommendations on chlamydia treatment need to be re-evaluated.

Previous studies that have reported an azithromycin treatment failure rate of 2-3% utilized test of cure by chlamydia culture which, in the last decade, has been replaced by more sensitive PCR testing [22]. Chlamydia treatment studies that have utilized PCR testing have reported much higher treatment failure rates of up to 8%; however these studies were not designed to reliably distinguish between re-infections and treatment failure [10,17]. Our study is one of the first to use both robust molecular microbiological testing and validated behavioural data so that treatment failure rates can be more accurately estimated. We hypothesize that the treatment failure rate will be closer to 8%.

If our hypothesis is correct and 8%, rather than 2-3%, fail chlamydia treatment with azithromycin, then nearly 3,000 women in Australia and 70,000 women in the USA were inadequately treated for chlamydia in 2011 [2,55]. Treatment failure will lead to persistent infection with a longer duration of infection and increased risk of complications as well as continued transmission in the population. Further, as chlamydia culture has been rarely undertaken over the last decade, there is little monitoring of chlamydia antibiotic susceptibility, and the role of antimicrobial resistance in treatment failure is unknown [35]. The ability to differentiate between re-infection and treatment failure is a strength of this study. Techniques used will include measuring azithromycin absorption in genital cells, chlamydia culture, genotyping, DNA sequencing and antimicrobial sensitivity determinations of the chlamydia isolates obtained. The results from this study will inform discussions about chlamydia treatment failure and help to establish whether 1 gram azithromycin, the most widely recommended chlamydia treatment internationally, is appropriate. If treatment failure is confirmed to be higher than previously estimated, then further chlamydia treatment trials to suggest changes to international treatment guidelines will be indicated.

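### The persistent-chlamydia subtype turns on a negative culture from a later recall visit and does not use the PCR scheduled at that visit, so women with no detectable organism by then can be labelled persistent

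*Protocol article*

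**What the plan says.** The subtypes apply only within treatment failure: "Treatment failure will be further classified as" one of three kinds (section on further classification of treatment failure). Under Primary outcome, a woman gets that far only "following detection of chlamydia on a self-collected high-vaginal specimen using a polymerase chain reaction" at day 28, 42 or 56, and then only if the strain and exposure conditions hold: "Detection of same MLST type without detection of Y chromosome DNA or any reports of unprotected sex will be classified as treatment failure".

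Within that group the persistent subtype has three conditions. The first is the drug level: "Azithromycin absorption shows adequate levels of azithromycin in the vaginal cells". The second and third come together: "the minimal inhibitory concentration (MIC) for the initial chlamydia culture is within reported range and the subsequent chlamydia culture is negative".

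The section on specimen collection and testing says that women who test positive again are telephoned, and continues: "These women will be requested to attend the clinic for treatment and further specimen collection". The last column of Table 1, headed "If PCR positive @ d28, 42 or 56", is that clinic visit. It marks culture, PCR, organism load, genotype and sequencing. The Culture section says that culture uses an endocervical swab taken by speculum, frozen and couriered to the laboratory.

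**The concern.** The subtype is meant to identify infection that survived treatment although the drug reached the tissue and the organism was susceptible. PCR-positive with culture-negative looks like the intended pattern, so a negative culture is not in itself a mistake. The difficulty is that the positive PCR and the negative culture come from different days and different sites, and nothing in the rule requires the organism to be detectable when the culture is taken.

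A negative culture at the recall visit can mean that the organism is present but does not grow, that neither organism nor DNA is there any longer, or that culture missed a viable infection. The rule gives all three the same label. The second does not fit the label, and it is the one that the scheduled PCR could pick out.

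At stake is how the study explains failure: poor absorption, persistence or reduced susceptibility. A persistence group that may include women with nothing detectable at the recall visit is weaker evidence that persistent infection accounts for azithromycin failure.

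**Working it through.** **Step 1. When each criterion is measured.**

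| Criterion for the persistent subtype | Specimen | When | Source |
|---|---|---|---|
| Adequate azithromycin level | Nurse-collected high-vaginal | Day 7 | Azithromycin absorption; Table 1 |
| MIC in reported range | Initial culture, endocervical | Day 0 | Further classification of treatment failure; Table 1 |
| Subsequent culture negative | Endocervical, frozen | Recall visit after a positive day 28, 42 or 56 swab | Culture; Table 1, last column |

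The earliest test of cure is day 28. The drug level therefore precedes it by at least 28 − 7 = 21 days and the baseline MIC by 28 days. Neither describes the organism at follow-up. Among failures who meet the first two criteria, the culture alone decides whether this label is given.

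**Step 2. What links the positive PCR to the culture.** The qualifying PCR is on a self-collected high-vaginal swab posted from home. The culture is on an endocervical swab taken after the result is known and the woman has been recalled. No interval between the two is stated or limited.

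**Step 3. Run a case through the rule.** Take a woman with a positive day 28 PCR, the baseline MLST type, no Y-chromosome DNA, no reported unprotected sex, an adequate drug level and an in-range MIC. At the recall visit both her PCR and her culture are negative. Every stated condition for the persistent subtype is met. The PCR result that argues against the label is collected but not consulted.

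**Step 4. Scale.** The plan's own figure comes first. For a half-width of 0.025 around 8%, n = 1.96² × 0.08 × 0.92 / 0.025² = 452.4, which agrees with the stated 450. Expected failures are 450 × 0.08 = 36. At the alternative risk of 3% given under Sample size estimates, they are 450 × 0.03 = 13.5.

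The documents give neither the share of failures meeting the drug-level and MIC criteria nor the share PCR-negative at return. I assume 80% for the first and 10–20% for the second:

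| Failure risk | Failures | × 0.80 | × 0.10 | × 0.20 |
|---|---|---|---|---|
| 8% | 36 | 28.8 | 2.9 | 5.8 |
| 3% | 13.5 | 10.8 | 1.1 | 2.2 |

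That is about 3–6 women at 8% and about 1–2 at 3%. If nobody is PCR-negative at return, the number is zero.

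**The case against.** The strongest case on the other side has five parts.

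- **Culture is only one criterion.** A reader might infer that a negative culture by itself defines the class, or that the class collects whatever culture failed to grow. The documents do not support that. Only same-strain, PCR-positive failures enter, and women with a low drug level or an elevated MIC do not meet this subtype's conditions whatever their culture shows. This limits the scope but leaves the gap, because the other two criteria predate follow-up.
- **Misclassification is only possible.** A reader might infer that cleared infections are in fact being labelled persistent. No clearance rate or swab-to-visit interval is given. A footnote to Table 1 says that test-of-cure PCR is run in real time, so the interval may be short. This stands: the text shows that the rule permits the error, not how often it occurs.
- **Missed cultures are not shown to be wrong labels.** The Discussion says that earlier studies "utilized test of cure by chlamydia culture which, in the last decade, has been replaced by more sensitive PCR testing", and a reader might infer that every viable infection missed by culture is a further error. But a viable same-strain infection with adequate drug and an in-range MIC still fits the words of the label, and neither of the other two subtypes would take her. Applying a miss rate for viable infections to all the remaining women would also leave no room for the non-culturable infections that the class seems meant to capture. I therefore put no number on this group.
- **The consequence is limited.** The statistical analysis uses the three-level outcome (failure, success, re-infection) and enters organism load, absorption and MIC directly. It plans no estimate of the subtype's share. This stands, and it keeps the point secondary.
- **An article condenses.** Detailed reading of the return-visit results could sit in a fuller document, and Figures 1 and 2 are not shown. By their captions, however, the figures cover failure and endpoint classification, not these subtypes. The article states a complete-looking rule, and that rule admits the wrong cases.

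**Conclusion.** The point holds in limited form. As written, the persistent subtype can include women in whom no organism is detectable at the recall visit, because the rule pairs a positive home PCR with a negative culture from a later day and another site and passes over the PCR scheduled with that culture.

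The size cannot be determined from the documents. The illustration of about 3–6 women at 8%, or 1–2 at 3%, rests wholly on the assumed 80% and 10–20%. With only about 36 or 13.5 failures expected in all, a few reassignments would still change the make-up of the subtypes.

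Only the secondary sub-classification is affected. Treatment failure itself is set by the test-of-cure PCR, strain typing and exposure evidence, so the primary proportion and its confidence interval do not change.

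**What to change.** - **Reword the persistent subtype.** Require the return-visit PCR to be positive, with the baseline type where typable, in addition to the negative culture from the same visit and the two existing criteria.
- **Report the others separately.** Show women whose return-visit PCR is negative under a heading such as *test-of-cure positive, not detected at return visit*. They remain treatment failures for the primary outcome.
- **Show the context.** Beside each culture result, give the return-visit organism load and the days from test-of-cure swab to culture swab. A separate low-load category is not proposed, since the documents give no threshold for one.
- **State the remaining limit.** A positive PCR with a negative culture does not by itself distinguish organisms that cannot be cultured from a culture that missed them, because PCR detects DNA and not viability.

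The cost is a small rewording plus recording one interval. The assays are already in the last column of Table 1, so no new specimen or test is needed. The drawback is that fewer women will receive the persistent label, in a group that is already small.

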### Specimen collection and testing

Participants will be asked to return to the clinic for follow up testing at day 7 so that the research nurse can collect further specimens. Thereafter, weekly high-vaginal specimens will be self-collected at home and mailed in a postage-paid envelope to the study centre. Participants will receive weekly short message service (SMS) prompts reminding them to return specimens and questionnaires and will be telephoned if they test chlamydia positive again throughout the study. These women will be requested to attend the clinic for treatment and further specimen collection. Table 1 outlines the number of specimens collected and the tests to be undertaken at each stage of the study.

### Chlamydia polymerase chain reaction (PCR)

Test of cure swab specimens collected on day 28, 42 and day 56 will be placed in Cobas® PCR Media (Roche Diagnostics) and will be tested in batches on COBAS 4800 CT/NG (Roche Diagnostics). The remaining eluted DNA from COBAS 4800 will be stored at −80°C until required for further assay. For specimens collected at other time points, swabs collected will be rotated for 30 seconds in 1 ml of phosphate buffered saline (PBS) and stored at −80°C until further testing required. Specimens will be subsequently extracted with MagNA Pure 96 (Roche Diagnostics) using 200 μl of the cellular suspension in conjunction with the total nucleic acid isolation kit. Eluted nucleic acid of 100 μl will be tested as required.

### Genotyping & quantification of organism load

Chlamydial fingerprinting will be conducted on specimens that are PCR positive at baseline and at test of cure. We will determine the organism load, identify the chlamydia serovar(s) (genovar) of each infection through a series of quantitative PCR assays to establish whether or not the genotype of the chlamydia detected in those women who have a repeat positive is the same as the type present at baseline [27]. Initial qPCR primers and probes have been designed to predict antigenic differences in major outer membrane protein (MOMP) to determine the serovar as previously described [27,36-38]. The primary chlamydia group-specific multiplex quantitative PCR will target conserved regions of the *ompA* gene specific to all chlamydia serovar groups, including the B group (serovars B, E, D, L1, and L2), C group (serovars A, C, H, I, J, K, and L3) or intermediate group (serovars F and G) serovars. This assay will enable quantification of organism load and will be used to direct serovar-specific PCRs to determine serovars present in the specimen, including possibility of mixed serovars [27,39].

Chlamydia organism load in each specimen will be quantified by comparing the crossing-threshold of each specimen to the crossing-threshold of a standard curve constructed by amplifying different known copy numbers of the *ompA* gene. The beta globin gene, present at one haploid copy per nucleated cells [40], will also be quantified using qPCR to assess specimen adequacy as well as to measure sampling variability between participants and specimens by correlation with the number of eukaryotic cells collected. The quantity of chlamydia will be divided by the number of eukaryotic cells and expressed as the number of organisms present per 100 eukaryotic cells [40].

Specimens from participants where the same serovar has been detected at baseline and follow up will undergo further discriminatory confirmation of relatedness using sequencing of *ompA* gene, as well as five house-keeping genes (*hctB,* CT058, CT144, CT172, and CT682 [*pbpB*]) utilizing a multilocus sequence typing (MLST) approach [28,29,41,42]. This will include the amplification and sequencing [29,43,44] followed by determining MLST type using *C. trachomatis* MLST database (mlstdb.bmc.uu.se).

### DNA sequencing to identify mutation in 23S rRNA gene

Each specimen will be subjected to DNA sequencing (as described above) of PCR-amplified region of the 23S rRNA gene flanking the positions 2057 and 2611. Presence of changes in three locations, A2057G, A2059G and T2611C (*E. coli* numbering), will be determined as they are associated with increased macrolide resistance [45]. The data arising from this experiment will be correlated with MICs as described below.

### Detection of Y chromosome

A separate swab will be collected each week and placed in 400 μl of PBS for Y-chromosome detection as evidence of unprotected sexual exposure. Real-time PCR directed at amplification of a region of the Y chromosome targeting SRY (sex determining region Y) will be conducted [25,26].

### Culture

Endocervical specimens collected by speculum examination will be used for chlamydia culture. The research nurse will place the swab immediately into culture medium, store at −80°C, and courier to the laboratory on dry ice for processing. Chlamydia isolates will be cultured on HEp-2 to propagate each isolate prior to progressing to MICs. Specimens will be prepared by vortexing before addition to 20 hour HEp-2 cultures in antibiotic free DMEM supplemented with 10% serum. Cultures will be incubated at 37°C, 5% CO_2_ for 48 hours and viable infectious chlamydia elementary bodies will be harvested by mild sonication. A serial dilution of the specimen cultured onto coverslips in 24 well plates with 20 hr growth 2 × 10^5^ HEp-2 cells to determine the viable infectious yield [46].

### Minimum inhibitory concentration (MIC)

MIC will be conducted by culturing chlamydia on 20 hr HEp-2 cells. HEp-2 cells will be used for all MIC determinations as they are the most relevant immortalised cell line (cervical), are widely used, and have previously been shown to have consistent performance in MIC assays when compared to other cell lines [35]. Low passage clinical isolates prepared above will be inoculated onto the HEp-2 cells at 2500 and 5000 IFU per well. Cultures will be centrifuged for 1 hr (1200 × g) to ensure equal infection rates. These inoculums will be used as they have previously been reported to be an appropriate dose to predict the MCC (minimum chlamydicidal concentration) and are adequate numbers to accurately assess the inclusions formed [35]. The antibiotic will be titrated into the infected cultures at 4 hours after addition of the chlamydia using a twofold dilution series from 140 g/ml to 0.008 g/ml (in fresh media with cycloheximide 1 g/ml). Antibiotic will be freshly prepared as per the manufacturer’s instructions for each experiment. The numbers of correctly formed inclusions will be determined by methanol fixing the coverslips at 30 hours and stained to allow clear visualisation and counting of the inclusions on the microscope (Chlamydia Cel, Vital diagnostics). The MIC will be defined as the concentration at which no typical inclusions can be seen on the entire coverslip by microscopy examination.

